### Procedure for unblinding if needed {17b}

Not applicable because it is not possible to blind the investigators or participants.

## Data collection and management

### Plans for assessment and collection of outcomes {18a}

During screening, sociodemographic and baseline information (including age, sex, contact information, and past medical history) will be obtained. The success of HP eradication will be assessed by stool antigen assays performed with the enzyme immunoassay method (EIA) 6 weeks following the completion of therapy [45]. Participants will be prohibited from using PPIs, antibiotics, H_2_ receptor antagonists, aspirin, herbal remedies, and probiotics for 8 weeks until the stool antigen testing. The stool antigen tests must be performed no later than 6 weeks + 3 days after the completion of therapy. The data on adverse events and compliance will be obtained face-to-face and documented using the data collection form no later than 3 days following the completion of therapy. The count of pills taken will be used to determine study drug compliance. The data will be obtained from two trained assistants who are instructed to collect the information in a consistent, reproducible manner, and the integrity of the data will be overseen by the principal investigator.

### Plans to promote participant retention and complete follow-up {18b}

Investigators will communicate with participants on a regular basis by phone and WhatsApp twice a week. They will utilize approaches such as notifications such as phone calls, texting (SMS), or WhatsApp to take the trial medicine and schedule meetings for stool antigen tests to improve participant engagement.

### Data management {19}

Two assistants will be in charge of data entry and data integrity by double-checking the data. All information will be entered digitally. A Microsoft Access database has data entry forms that will allow the assistants to select specific data from a list of valid data, while what will be stored in the data tables are only the codes that express this data. A main researcher will check the data entry to ensure that the data is entered into the correct fields. Participant files must be stored in a secure location in numerical sequence. After the study is completed, the files will be kept in storage for 3 years. A password system will be used to restrict access to the study data.

### Confidentiality {27}

All data obtained for this trial will be encoded with unique patient identities, ensuring that no individual patient can be recognized. Patient records shall be reviewed only when required and in accordance with Damascus Hospital’s Ethics Committee requirements. Any records relating to participant identification are concealed and will not be made public, to the extent permitted by applicable laws and regulations.

### Plans for collection, laboratory evaluation, and storage of biological specimens for genetic or molecular analysis in this trial/future use {33}

The researchers will collect gastric mucosal biopsy samples, and after 4 weeks + 3 days of end-of-treatment, they will get a stool sample for the HP infection test. For the specimens that bear unique patient identities, a standard methodology will be followed. All biopsies will be sent to the referring hospital’s central pathology laboratory, while stool samples will be sent to the same referring hospital’s central laboratory.

## Statistical methods

### Statistical methods for primary and secondary outcomes {20a}

To compare the eradication rate of HP, we will use the ITT analysis (all individuals who got at least one dosage of the trial treatment) and PPA (all individuals who complied and were tested again using a stool antigen test). We will use the *χ*^2^ test, which will be used for nominal variables, such as sex, treatment protocol, treatment outcome based on stool antigen tests, each adverse event, smoking, and alcoholic status, to determine if there is a relationship between the treatment protocol and the result of the treatment for both the primary and secondary outcomes [50]. We will use the *t*-test to compare the means of the continuous variable, such as patient’s age, with the normal distribution for both the primary and secondary outcomes [51]. The difference in eradication rates between the two treatment regimen groups can be assessed by a two-sided 95% confidence interval (CI). Individuals whose stool antigen tests have not been retested including dropouts will be considered treatment failures. The statistical significance level is a *P*-value of 0.05.

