
## Objectives {7}

The main objective of this study is to compare the eradication rate of HP infection using levofloxacin-based sequential therapy against levofloxacin-based concomitant therapy using an intention-to-treat analysis (ITT) and a per-protocol analysis (PPA).

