## Trial design {8}

This is a single-center, prospective, superiority randomized, open-label, active-controlled clinical trial with a 1:1 allocation ratio. Figure 1 shows a trial flow chart.

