#### Criteria for discontinuing or modifying allocated interventions {11b}

The safety of HP eradication therapy is well known, with the most common adverse events being taste disturbance, diarrhea, nausea, and abdominal pain. The vast majority of adverse events are minor and transient [43]. According to estimates, just 1.3% of patients terminate treatment due to adverse events [44]. Six weeks after ending treatment, all patients will visit the central laboratory of our hospital and undergo stool antigen tests using the enzyme immunoassay method (EIA) [45]. In our research, when individuals report adverse events, the investigators will examine them. The experiment’s drugs may be withdrawn for any of the following reasons: (1) significant adverse events that are considered unsuitable for continuing treatment, such as events that are life-threatening, necessitate inpatient hospitalization, result in persistent or significant disability or incapacity, or may necessitate medical or surgical intervention to prevent one of the outcomes listed above; (2) inability to comply with the trial procedures. Individuals may withdraw from the trial at any time for any reason. The reasons for withdrawal will be noted if individuals indicate them.

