### Sample size {14}

We will conduct this as a superiority clinical trial, and the calculation of the sample size is based on the primary outcome, which is the eradication rate of HP infection using ITT. According to a meta-analysis, Kale-Pradhan et al. reported the eradication rate of a sequential levofloxacin-based treatment regimen as 87.8% (P2 = 0.877) [40], while the eradication rate of a concomitant levofloxacin-based regimen was based on the results of a randomized clinical trial conducted in Syria and was 82.05% (P1 = 0.8205) [37]. We applied the following statistical hypotheses: (1) 80% power (*β* = 0.2); (2) the 5% level of significance (*α* = 0.05); and (3) the superiority margin is 10% (*δ* =  − 0.10) and (*ε* = 0.20). Given that *Zα* and *Z*_*β*_ are 1.64 and 0.845, respectively; (4) the ratio of case to control is equal to one (*K* = 1). The sample size formula of the two parallel superiority designs resulted in 64 patients as a sample size for each parallel [47, 48]. We also added 15% for possible dropouts, making the final sample size 150 patients. For more information, please check Additional file 1.

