### Implementation {16c}

Once a researcher has obtained the patient’s informed consent, they will contact the independent assistant to get the allocated treatment regimen.

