## Assignment of interventions: blinding

### Who will be blinded {17a}

It is challenging to blind the participants and the researchers in this open-label trial. However, throughout the whole trial, laboratory medical professionals, data collectors, and data analysts will remain blinded to the therapy allocation. The allocation information will be hidden on a data collection form for adverse events and compliance, and data collectors are not permitted to inquire about participants' regimens.

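### The set called ITT requires at least one dose; in this open-label trial that can bias the primary comparison, in either direction, if non-starting differs by arm

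*Protocol article*

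**What the plan says.** All references are to the protocol article.

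- Statistical methods for primary and secondary outcomes {20a} fixes membership of the set: "ITT analysis (all individuals who got at least one dosage of the trial treatment").
- Sample size {14} ties the calculation to the primary outcome, "which is the eradication rate of HP infection using ITT". Objectives {7} states the main comparison as "using an intention-to-treat analysis (ITT) and a per-protocol analysis (PPA").
- Implementation {16c}: once consent is given, researchers act as follows: "they will contact the independent assistant to get the allocated treatment regimen".
- Who will be blinded {17a}: "It is challenging to blind the participants and the researchers in this open-label trial".
- Criteria for discontinuing or modifying allocated interventions {11b}: "Individuals may withdraw from the trial at any time for any reason".
- The missing-outcome rule in {20a}: "Individuals whose stool antigen tests have not been retested including dropouts will be considered treatment failures". Methods for additional analyses {20b} repeats the failure rule for patients who are not retested.
- Exclusion criteria, item 7, under Eligibility criteria {10}, also says that a participant who takes one of the listed restricted treatments during the trial or follow-up is to be excluded. It does not say whether this means from treatment, from follow-up or from an analysis set.

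**The concern.** An intention-to-treat comparison keeps everyone who was randomised, so that the arms differ only by chance and by allocation. A set that begins with the first dose is defined by something that happens after allocation. That is harmless only when starting cannot depend on the arm.

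Here it can. The patient and the researcher both know the regimen before the first dose, the two regimens are visibly different, and withdrawal is free at any time. A patient who hears the allocation and never starts falls outside the stated set. One who takes a single dose and then disappears is inside it and counts as a failure. If the first kind of patient is commoner in one arm, that arm's reported rate is raised relative to what allocation to it achieves. The trial asks which regimen works better as empirical first-line therapy, and patients who do not start are part of that answer.

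**Working it through.** **Inputs.** From Sample size {14}: sequential p2 = 0.877 (the percentage is printed as 87.8%), concomitant p1 = 0.8205, margin δ = −0.10, z values 1.64 and 0.845, 64 per arm, 15% dropout, 150 in total. The article gives no non-start rate; the rates a2 (sequential) and a1 (concomitant) below are assumptions.

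**Step 1: the plan's own figure.**
n = (1.64 + 0.845)² × [p1(1 − p1) + p2(1 − p2)] / [(p2 − p1) − δ]²
= 6.1752 × (0.1473 + 0.1079) / 0.1565² = 64.3, printed as 64.
With dropout, 64 / 0.85 = 75.3 per arm, or about 150 in total. The printed figures reproduce. They do not depend on which analysis set is chosen, so they neither support nor weaken this point.

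**Step 2: the shift from leaving out non-starters.** Apply p2 and p1 to dosed patients, and count non-starters as not eradicated.

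- Dosed set: p2 − p1 = 0.877 − 0.8205 = 0.0565, or 5.65 points.
- All randomised: p2(1 − a2) − p1(1 − a1).
- Shift = dosed minus all randomised = p2·a2 − p1·a1.

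| Assumed a2 (sequential) | Assumed a1 (concomitant) | Shift, points | All-randomised difference, points |
|---|---|---|---|
| 0% | 0% | 0 | 5.65 |
| 5% | 5% | 0.05 × 5.65 = 0.28 | 5.37 |
| 2% | 1% | 1.754 − 0.8205 = 0.93 | 4.72 |
| 1% | 2% | 0.877 − 1.641 = −0.76 | 6.41 |
| 5% | 1% | 4.385 − 0.8205 = 3.56 | 2.09 |
| 1% | 5% | 0.877 − 4.1025 = −3.23 | 8.88 |

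A positive shift means that the dosed set overstates the sequential advantage; a negative shift means that it understates it. The last two rows are 3.56 / 5.65 = 63% and 3.23 / 5.65 = 57% of the planned difference.

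**Step 3: scale.** At 75 per arm, 5% is about 4 patients and 1% about 1. The standard error of the difference is √(0.2552 / 75) = 5.8 points at 75 per arm and √(0.2552 / 150) = 4.1 points at 150 per arm.

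**The case against.** **The missing-outcome rule may already cover these patients.** It names dropouts, and a patient who never starts could be called one. A reader might also go the other way and infer that the two rules contradict each other. Neither reading is secure. One sentence decides who is in the set and the other decides how an untested member is scored, so they can coexist. The failure rule does not override an explicit membership rule, and nothing else in the article expressly returns undosed patients to the set. If the authors do mean to count them, the wording is ambiguous and the same edit settles it.

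**No harm has been shown.** This stands. The 1.3% in {11b} is stopping because of adverse events, and the 15% in {14} is an allowance for all dropout; neither is a non-start rate. Face-to-face instruction at the first appointment and twice-weekly contact may keep non-starting low. The Discussion does voice a worry about the change of drugs between weeks, but that concerns compliance, not starting.

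**The illustrated shifts lie within sampling error.** They do: even 3.6 points is below one standard error at either sample size. But sampling error shrinks as patients are added, and this bias does not.

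**An unseen analysis plan may define the sets properly.** It may, but the point concerns a definition that this article states, not one that it omits.

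**Conclusion.** The point holds in a limited form. The set labelled ITT is a modified-ITT set, it carries the primary comparison, and in this open-label design it can bias that comparison.

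A reader might infer that randomisation is broken, or that the plan systematically flatters one regimen. The article supports neither. Bias of any size needs non-starters, and material bias needs them to differ by arm; open allocation makes that possible but does not show it. The direction is also open: an excess in the sequential arm inflates its advantage, and an excess in the concomitant arm hides part of it.

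The size is therefore unknown. Under the assumed rates it runs from zero, through 0.3 points (5% in both arms) and 0.8 to 0.9 points (2% against 1%), to 3.2 to 3.6 points (5% against 1%), against a planned 5.65. These figures assume that the planned rates hold among dosed patients, that non-starters count as not eradicated, and that those who start would respond the same whatever the non-start rate. The change is worth making because the non-start rate cannot be known in advance and the correction is almost free.

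**What to change.** 1. In {20a}, define ITT as all randomised participants, analysed in the arm allocated, whether or not a dose was taken. Untested patients remain not eradicated under the existing rule.
2. Keep the at-least-one-dose set only as a sensitivity analysis, labelled modified ITT.
3. Reconcile item 7 of the Exclusion criteria with this definition. As an analysis matter, participants excluded after randomisation for using a restricted treatment should leave the per-protocol set only and stay in the ITT set. Without this, editing {20a} alone leaves a second post-randomisation exclusion in place.

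The cost is a short edit in two sections and slightly lower reported eradication rates if some patients never start. If everyone starts, the change of definition in {20a} alters no result. The printed 64 per arm, 150 in total and the ceiling of 300 are unaffected. Trial status reports that no patient had been enrolled at version 3, so at that stage the change could be made without sight of outcome data.

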### Interim analyses {21b}

We intend to do a subgroup analysis of the eradication rate of the rescue protocol following first-line therapy failure. We expect rescue treatment to be similarly effective in both groups. The overall eradication rate of the rescue protocol and the relationship between the first-line treatment protocol and the outcome after using the rescue regimen will be assessed by using the *χ*^2^ test, with a two-sided 95% CI of the difference in eradication rates between the two groups. The statistical significance level will be set at a *P*-value of 0.05.

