### Outcomes {12}

The trial’s primary outcome is the percentage of patients who have successfully eradicated HP infection. This will be established based on the findings of stool antigen testing using the enzyme immunoassay method (EIA) [45], 6 weeks after the completion of the first-line treatment phase of the levofloxacin-based concomitant or levofloxacin-based sequential treatment regimen. The HP stool antigen test is an accurate approach for confirming HP eradication after the fourth week following treatment, based on a comprehensive evaluation of 25 reports involving 2078 individuals who examined the HP stool antigen test for confirmation of HP eradication. The sensitivity, specificity, positive predictive value (PPV), and negative predictive value (NPV) were as follows: 88.3%, 92%, 75.1%, and 94.8% [46].

The secondary outcomes are:

The rate of HP eradication of rescue treatments and total eradication rates among the levofloxacin-based concomitant and levofloxacin-based sequential treatment regimens; (2) the type and frequency of adverse events, as well as the rate of compliance, between the levofloxacin-based concomitant and levofloxacin-based sequential treatment regimen groups.

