### Methods for additional analyses (e.g., subgroup analyses) {20b}

The overall eradication rate of the rescue protocol and the eradication rate according to the first-line treatment protocol and outcome after using the rescue regimen will be assessed by using the *χ*^2^ test with a two-sided 95% CI of the difference in eradication rates between the two groups. The statistical significance level will be set at a *P*-value of 0.05. Patients who have not had their stool antigen tests reexamined will be deemed treatment failures, i.e., “not eradicated,” in the statistical analysis. Strategies will be put in place to increase follow-up, promote adherence, and prevent missing data. We will report and qualitatively compare the reasons for non-adherence for each randomization group.

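### Rescue eradication is tested between first-line arms in only about 22 to 45 first-line failures: the contrast is not randomised and is too imprecise to bear on the expected similarity

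*Protocol article*

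**What the plan says.** Interim analyses {21b} describes a subgroup analysis of rescue eradication in patients whose first-line treatment failed. It states: "We expect rescue treatment to be similarly effective in both groups". It then relates rescue outcome to first-line regimen with a chi-square test at P = 0.05 and a two-sided 95% CI of the difference. No timing, stopping rule or similarity margin is given.

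Methods for additional analyses {20b} plans nearly the same thing again, a chi-square "test with a two-sided 95% CI of the difference in eradication rates between the two groups", and counts patients without a repeat stool test as not eradicated.

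Outcomes {12} lists as secondary: "The rate of HP eradication of rescue treatments and total eradication rates among the levofloxacin-based concomitant and levofloxacin-based sequential treatment regimens". Statistical methods {20a} applies the chi-square test to primary and secondary outcomes generally. The Discussion gives high importance to estimating the rescue rate, so this result is likely to be reported and used.

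**The concern.** Rescue is offered only after first-line failure, and first-line failure is the trial's primary outcome. If one regimen works better, its failures are a different and more selected set of patients from the other regimen's failures. A difference in rescue success between these two sets mixes any effect of the first-line choice with selection, and a larger sample does not remove the selection.

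The set is also small. A difference test in a few dozen patients says little either way about an expectation of similar efficacy, and without a margin there is no standard against which similarity could be judged.

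The placement is a further difficulty. Taken literally, an analysis under the interim heading would show first-line failure counts by arm during an open-label trial that has no data monitoring committee.

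At stake is a secondary result: the report could carry a P-value for a non-randomised contrast, while the randomised strategy comparison (first line plus rescue) gets no explicit between-arm plan in the two sections that deal with rescue.

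**Working it through.** **Inputs from the documents.** Sample size {14}: concomitant eradication "was 82.05% (P1 = 0.8205"); sequential eradication printed as both 87.8% and 0.877; "the 5% level of significance"; z values that "are 1.64 and 0.845, respectively"; "the superiority margin is 10"% (δ = −0.10); 64 per arm, 150 in total after 15% dropout. Trial design {8}: 1:1 allocation. Abstract: recruitment of up to 300. The rescue rate is not given; 50% to 90% is assumed throughout.

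**1. The plan's own figure.** n = (z_α + z_β)² [p1(1−p1) + p2(1−p2)] / ((p2−p1) − δ)²
= (1.64 + 0.845)² × [0.8205×0.1795 + 0.877×0.123] / (0.0565 + 0.10)²
= 6.175 × 0.2552 / 0.02449 = 64.3 per arm (63.3 with 0.878).
This reproduces 64. Then 128/0.85 = 150.6, against 150 stated. The planning rates are therefore the right basis for counting failures.

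**2. Expected first-line failures**, n(1−p):
- N = 150: 75×0.1795 = 13.5 and 75×0.123 = 9.2, together 22.7 (13 v 9 in whole patients, rounding down).
- N = 300: 150×0.1795 = 26.9 and 150×0.123 = 18.4, together 45.4 (27 v 18).

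The planned failure proportions are about 18% and 12%, so entry to the rescue comparison depends on arm.

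**3. Precision.** Half-width = 1.96 √[r(1−r)(1/a + 1/b)], with the same rescue rate r in both arms:

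| r | 13 v 9 | 27 v 18 |
|---|---|---|
| 50% | 42.5 points | 29.8 points |
| 80% | 34.0 points | 23.9 points |
| 90% | 25.5 points | 17.9 points |

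**4. Power of the two-sided chi-square test at 0.05**, by exact enumeration of both binomials. Each range covers which arm has the lower rate:

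| Rescue rates | 13 v 9 | 27 v 18 |
|---|---|---|
| 80% v 50% | 32% to 40% | 55% to 56% |
| 80% v 60% | 17% to 24% | 28% to 30% |

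**5. What showing similarity would need.** Two one-sided tests at 0.05, 80% power, true rate 80% in both arms: n per arm = 2×0.8×0.2×(1.645 + 1.282)²/margin². This gives about 275 failures per arm for a 10-point margin and 69 for a 20-point margin. The trial expects 9 to 27 per arm.

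**6. The randomised alternative.** Total eradication = p + (1−p)r, if every failure takes rescue. At r = 80% this is 0.8205 + 0.1795×0.8 = 96.4% and 0.877 + 0.123×0.8 = 97.5%. The half-width 1.96 √[t1(1−t1)/n + t2(1−t2)/n] is 5.5 points with 75 per arm and 3.9 points with 150. The expected difference is only about 1.1 points, so this comparison is not powered either. It does keep the randomised groups.

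**The case against.** The strongest reply is that the quoted sentence is an expectation, not an equivalence hypothesis or a decision rule. A reader might infer that a non-significant P will be reported as proof of similarity. The documents do not say so, and the planned 95% CI would display the imprecision. That stands. What remains is that an expectation of similarity is paired with a difference test and no margin.

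A reader might also infer that the test or interval is invalid at these counts. That is not supported. By enumeration at an 80% rescue rate, the chi-square type I error is 5.1% at 13 v 9, 4.9% at 14 v 9 and 4.6% at 27 v 18. The simple Wald interval covers 88.8%, 92.5% and 93.4% respectively, so the poor figure turns on one patient, and the protocol names no interval method. The weakness is selection and precision, not test size.

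Using only the smaller count would overstate the problem. The abstract plans up to 300 patients, so the range 22 to 45 is the fair statement; the conclusion is the same at both ends.

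Much of the remedy is already listed: total eradication by regimen is a secondary outcome, and the overall rescue rate is in both analysis sections. What is lacking there is a statement that the between-arm inference rests on total eradication.

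Finally, a reader might infer a planned interim look. The text calls itself a subgroup analysis, gives no timing and is nearly repeated under {20b}, so text placed under the wrong template heading is the likelier explanation. In an open-label trial the treating investigators also see individual failures anyway. This leaves a point of wording, cheaply resolved.

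**Conclusion.** The point holds as a secondary-outcome matter that should be corrected. The by-arm rescue test compares groups selected after randomisation by the primary outcome. With about 22 to 45 failures, it cannot support or refute the stated expectation: a true gap of 80% v 50% would be missed in 60% to 68% of trials at N = 150 and about 45% at N = 300.

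This rests on the protocol's planning rates and on assumed rescue rates of 50% to 90%. The number actually given rescue may differ from the number of failures, because patients without a repeat test count as failures but may never take rescue. The primary analysis is unaffected, and the documents do not support a claim that similarity will be asserted.

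**What to change.** In Interim analyses {21b} and Methods for additional analyses {20b}:

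- State that the between-arm inference on treatment strategy is the total eradication rate (first line plus rescue) in all randomised patients, as already listed in Outcomes {12}.
- Report rescue eradication pooled over arms with an exact 95% CI.
- Report rescue eradication by first-line arm descriptively, with a Newcombe or exact interval for the difference, no test and no claim of similarity.
- Move the analysis out of the interim section and state that it is run once, after all follow-up is complete.

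The cost is a change of analysis wording and the loss of one underpowered secondary P-value. The sample size, data collection and primary analysis do not change.
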